#### Control condition

Parents assigned to the active comparator condition receive the same information as the experimental conditions regarding nutritional guidelines for young children and effective/ineffective parental feeding practices. However, this control group does not have access to interactive activities (e.g., quizzes) or self-regulation strategies during and between sessions (e.g., tailored feedback, goal setting, monitoring of the child’s food intake, and parental feeding practices).

#### Development of the *SmartFeeding4Kids* app

We designed and developed an application in Portuguese, the *SmartFeeding4Kids app*, to deliver all the intervention components and manage the trial. It can be used on web browsers or as an app on a mobile device and includes seven sessions that cater components from randomization, onboarding, 24 h food recall, delivery of information, personalized feedback to data collection (e.g., study questionnaires), and logging. Parents are guided through the program with new contents unblocked depending on the previous step and time.

The application was designed to be appealing and engaging. The visual design includes lively colors and several professional drawings of vegetables and fruits as characters (Fig. 3). Information boards are presented as slideshow animations where these characters give textual feedback illustrated with carefully designed visualizations. *Aba*, an avocado avatar, welcomes and accompanies parents in the application, guiding, informing, and motivating them through the sessions. Charts are presented to illustrate each session’s performance based on food diaries. To further fuel parents’ engagement, badges are given when they complete pre-defined achievements. Examples of badges are finishing a session, interacting with content, and daily logins, among others. In addition, to promote discoverability, we have introduced hidden rewards as special badges that are not visible before being won (e.g., a badge for filling the food recall meals along the day instead of all at the same time). Notifications and reminders are automatically sent via email to congratulate users for their performance, remind them of pending tasks, and announce new content.

**Fig. 3 Fig3:**
[figure not shown]
*SmartFeeding4Kids*
*app* features (from the upper left edge to the lower right edge of the figure). (1) General view of the program: sessions’ sequence. (2) Child’s 24-h food intake: selection of the number of portions eaten by the child in that day, regarding a specific food/beverage. (3) Nutritional information content (session 1). (4) Aba’s intervention: examples of verbalizations regarding ineffective feeding practices (e.g., pressure to eat). (5) Evaluative feedback: information about the number of portions of sugar-sweetened foods/beverages and vegetables eaten by the child in the day(s) recorded. (6) Goal setting: list of theme-related goals proposed to parents at the end of session 1

The application was iteratively co-designed within a team of psychologists, engineers, designers, and a nutritionist. Starting from the program sessions and elements, the team went from discussing low-fidelity prototypes to iterating over high-fidelity increasingly functional ones in a process that lasted over a year. A workshop was conducted with psychologists and nutritionists to create a set of personas and daily scenarios that guide and question the design decisions of the platform, particularly regarding the engagement of the participants and dealing with the program’s demand. Along with several iterations among the team and a pilot study with 12 participants, the application was fine-tuned to improve usability and adherence. This process was pivotal to adapt the onboarding process, making *Aba* (the avatar) more pervasive in the application and adjusting the rewarding mechanisms to be balanced (e.g., number and type of badges and respective points awarded). Most of the iterations were done over how each session should be presented, with food recall being the most demanding one to make usable.

### Participant recruitment and eligibility criteria

Recruitment will be conducted out nationally; participation is open to all parents of 2 to 6-year-old children living in Portugal. Information about the program and how to participate in the study will be shared through social networks (e.g., Facebook, Twitter, Instagram) and online groups attended by parents. A brief multimedia presentation about the intervention will be disseminated in parents’ meetings at collaborating local childcare facilities. We will also contact health professionals in primary health care centers and pediatric consultations to ask them to disseminate the intervention among parents they think could benefit from the program’s participation.

Participants are eligible to participate if (a) they are a parent/caregiver of one 2- to 6-year-old child at baseline (if the parent has two children in this age group, the parent is instructed to focus on the child that raises more concerns about their health habits, as reference); (b) have a mobile phone or computer/tablet with access to the internet; and (c) are fluent in Portuguese.

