### Power and sample size

Statistical power analysis was performed for sample size estimation based on published data regarding this topic using G*Power 3.1.9.2. For our repeated measures within-between group comparison study, we used Cohen’s *f* criteria and considered a small effect size of 0.15 [8, 31], an alpha equal to 0.05, and power of 0.80 for a two-group with four repeated measures design (with a moderate correlation pattern between time measurements of 0.35). The sample size needed is approximately 130 participants (i.e., 65 parents in each of the two-arm groups), but the total sample size was adjusted to account for a dropout rate of 50% [32, 33]. Therefore, the sample will be collected until 130 participants in each group (*N* = 260) enroll in the study. Our proposed sample size will also be adequate for multilevel modeling with level 1 repeated measures nested within level 2 individuals, by assuring a minimum of 50 individuals required for level 2 [34].

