### Randomization process

The random sequence generation process and the participants’ allocation to the intervention conditions will be run automatically by the online platform. After completing the baseline assessment, parents will be randomized and allocated to one of the conditions through an automated computerized randomization program, with an equal allocation ratio (1:1); the online intervention will be immediately available for parents after the allocation.

Parents will be blinded to which condition they were assigned during the trial. Participants are aware that the two interventions will be run and compared, and the tasks involved in each will be summarily reported, but they are not informed about the study’s hypothesis. The use of an active comparator intervention as a control condition will reinforce the blinding mechanism: parents will receive a similar intervention regarding the sequence of contents, duration, and the information available, but without the behavior change techniques intended to change parents’ and children’s behaviors (i.e., knowledge-based intervention). Researchers will be blinded to group allocation. Because of the intervention’s nature, which is programmed to be delivered automatically by the online platform according to the parent’s pace and answers, researchers do not participate directly in the intervention and cannot change its course.

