### Outcome measures

#### Primary outcome measures

##### Children’s dietary intake

Children’s dietary intake is evaluated through an online 24-h food recall developed for this study (*SmartKidsDiet24*). Parents are asked to record all the foods eaten by the child in their presence, foods eaten in meals prepared or offered by parents (e.g., snacks sent to school), or foods that parents are sure that the child ate in the specific days chosen by the app. Foods offered by childcare facilities are not recorded. The app guides parents in registering food and portions for the five main meals (breakfast, morning snack, lunch, afternoon snack, dinner), but it is possible to add an extra meal or snack. Parents also report the time (hh:mm) the food or meal was eaten. The *SmartKidsDiet24* uses an electronic food composition database developed by INSA (National Institute of Health Doutor Ricardo Jorge), compiling several food information sources (i.e., analytical studies, scientific literature, label information, other food composition tables, nutritional composition calculation for specific recipes according to the EuroFIIR method) adapted to the Portuguese diet. To better comply with the intervention aims, the database was updated with sugar-sweetened foods/beverages and other processed foods frequent in Portuguese children’s diet and foods included in vegetarians and vegan diets (e.g., dairy and meat substitutes). The *SmartKidsDiet24* uses the child’s hand as a portion size tool [35] to estimate the food quantities and follows the recommendations for 24-h food recall dietary assessment implementation [36]. Parents are shown which meals have already been registered (e.g., green color instead of gray). When a meal is selected, parents have access to the list of foods previously added to that meal. When adding new foods, parents have two options: search by name (with auto-complete) or by food category. In the end, parents are asked if they want to continue adding others foods to that meal. They are also alerted to remember to add complementary items (e.g., chocolate in the milk). Data regarding the mean number of portions of vegetables, fruit, and sugar-sweetened foods and beverages registered on 3 days will be extracted from the database and analyzed separately as primary outcomes. Time points are as follows: baseline, immediately after the intervention, 3 months after the intervention, 6 months after the intervention.

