Possible limitations of our study protocol include the following: We anticipate most participants to be highly interested and motivated parents, with children with fewer feeding issues, possibly with a higher education level. We also expect most participants will be mothers. Although this is a common issue in parental nutrition interventions, children’s dietary patterns can be influenced by the other caregivers’ practices and the overall home food environment. Only the enrolled participant can complete the tasks and answer the questionnaires and food records. Also, all the measurement outcomes are reported by parents, including the objective measures (i.e., 24-h food recall, children’s and parents’ BMI), and those reports rule the self-regulatory strategies throughout the sessions. The RCT’s intervention arm is quite demanding due to the regular monitoring between sessions and the tasks required during the sessions. This experience can be challenging for some overwhelmed, time-constrained, or less motivated parents and might contribute to a high dropout rate. Also, a lack of direct contact with the research team can decrease parents’ involvement in the program. Although a design with an intervention arm and an active control condition comply with high-quality methodological standards, it also can lead to a less-expressive difference between conditions.

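### Two caregivers of the same child can each enrol and be randomized separately, so one child's diet can be an outcome in both arms (probably rare, cheap to prevent)

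*Protocol article*

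**What the plan says.** Under Participant recruitment and eligibility criteria, the Protocol article lists three conditions. Criterion (a) is that "they are a parent/caregiver of one 2- to 6-year-old child at baseline"; (b) and (c) concern a device with internet access and fluency in Portuguese. The recruitment sentence in the same section adds that "participation is open to all parents of 2 to 6-year-old children living in Portugal". One family situation has its own rule: "if the parent has two children in this age group, the parent is instructed to focus on the child that raises more concerns" about health habits.

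Under Randomization process, "parents will be randomized and allocated to one of the conditions through an automated computerized randomization program", in a 1:1 ratio. Data management ties each participant's data to a personal account. No section links accounts by child or household.

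The dietary primary outcomes come from a 24-hour recall: "Parents are asked to record all the foods eaten by the child in their presence", together with food the parents supplied or are certain was eaten. Power and sample size describes the multilevel structure as "level 1 repeated measures nested within level 2 individuals". The Discussion accepts that "children’s dietary patterns can be influenced by the other caregivers’ practices and the overall home food environment", and reserves each account's tasks and records to the person who enrolled.

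**The concern.** The authors considered one parent with several children, but not several caregivers with one child. Both partners in a couple meet (a) to (c), and the platform allocates each of them on completing baseline, with nothing to recognise that they report on the same child.

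If the two fall in different arms, the control parent lives in a household where the other parent is using the experimental program. By the article's own account, the child's diet responds to other caregivers and to the home food environment. The control record is then partly exposed to the intervention, and the dietary contrast from that pair is pulled toward zero. Analysis cannot recover a contrast lost in this way, so the time to act is before allocation.

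The vegetable, fruit and sugar-sweetened outcomes are affected. The other three primary outcomes are the parent's own feeding-practice scores, so the argument that one child is counted twice does not apply to them.

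**Working it through.** **Step 1. The plan's own figures.** The dropout step reproduces: 130 / (1 − 0.50) = 260. The 130 itself does not come out of the usual repeated-measures formulas with f = 0.15, four measurements, correlation 0.35, alpha 0.05 and power 0.80:
- Group-by-time interaction, noncentrality f²·N·4 / (1 − 0.35): N = 82.
- Between-group test, noncentrality f²·N·4 / (1 + 3 × 0.35): N = 182.

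That is a separate matter, and the present point does not depend on it.

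**Step 2. Does the text admit a couple?** Take a mother and father of one 4-year-old.
- Eligibility: each is a parent of a child aged 2 to 6, so each passes (a), and nothing in (b) or (c) separates them.
- The multiple-children rule concerns one parent with two children, so it does not apply.
- Randomization: each is allocated individually once baseline is complete.
- Data: two accounts, not linked.
- Restriction on who uses an account: met, since each parent uses their own.

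No stated rule stops the second enrolment.

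**Step 3. Expected dilution.** Let m couples share a reference child among N participants, so s = 2m/N. If the two allocations are independent and 1:1, half of the pairs are expected to split, giving m/2 split pairs, or m people. As a share of the sample this is m/N = s/2. If a split pair shows no between-arm difference in the child's diet, the arm difference is multiplied by (1 − s/2). The values of s are assumptions. With N = 260:

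| s | People in couples | Pairs m | Expected split pairs | Attenuation s/2 |
|---|---|---|---|---|
| 5% | 13 | 6.5 | 3.25 | 2.5% |
| 10% | 26 | 13 | 6.5 | 5% |
| 20% | 52 | 26 | 13 | 10% |

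**Step 4. What this does to power.** Multiply f = 0.15 by (1 − s/2) and keep 130 analysed, with the same share s among them:

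| s | Diluted f | Power, interaction test | Power, between-group test |
|---|---|---|---|
| 0 | 0.150 | 0.957 | 0.660 |
| 5% | 0.146 | 0.947 | 0.638 |
| 10% | 0.1425 | 0.935 | 0.615 |
| 20% | 0.135 | 0.906 | 0.569 |

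**Step 5. Standard errors.** Code the arms z = +1 and −1. With equal arms the difference in means is (2/N)·Σ z·y, and its variance is (4/N²)·[Nσ² + 2·Σ over pairs of z₁z₂c], where c is the covariance between the two partners' records. A same-arm pair adds 2c and a split pair subtracts 2c. Under independent 1:1 allocation z₁z₂ averages zero, so the two kinds of pair offset in expectation. Leaving out the household level therefore has no systematic direction, although the realised mix of pairs can tip it either way.

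**The case against.** The strongest reply is that this is silence, not a misstatement. A duplicate check may exist in the platform or in the consent form, neither of which is shown. The Discussion's contrast between the enrolled participant and the child's other caregivers suggests that one caregiver per child was intended. The article expects mostly mothers and calls the experimental arm demanding. For s = 20%, 26 couples would have to enrol, with both partners completing the questionnaires and three recall days before allocation.

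Much of this stands. The frequency is unknown and probably low, and an unreported check cannot be excluded. It does not remove the point, because the article states its eligibility criteria and its unit of randomization, and together they admit the couple. The Discussion's restriction governs who uses an account, not who may open one.

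A reader might infer more than the documents support:
- That the child's two records are nearly identical. Each parent reports food eaten in their own presence, supplied by parents or known for certain, and the app picks the baseline recall days at random. The records overlap but need not agree, so zero contrast is a worst case.
- That standard errors will be too small because a same-arm couple counts one child twice. Split pairs act in the opposite direction, and in expectation the two offset.
- That blinding collapses when a couple sees both versions. Participants are already told that two interventions are compared and what tasks each involves, so the added harm is marginal.

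**Conclusion.** The gap is real and minor. As written, the plan lets two caregivers of one child be randomized to different arms, which dilutes three of the six primary outcomes. The expected dilution is at most s/2, that is 2.5%, 5% and 10% for s = 5%, 10% and 20%. This rests on three assumptions: a value of s that the article does not give, independent 1:1 allocation of the two partners, and no dietary contrast at all within split pairs. At the low end the loss of power is about one to two percentage points.

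The documents do not show that any couple has enrolled, and they do not support a claim of systematic standard-error bias. It earns mention because dilution cannot be undone after allocation, while prevention costs little.

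**What to change.** Add to the eligibility criteria that only one caregiver per reference child or household may be randomized. Enforce it before allocation with one registration question asking whether another caregiver of this child has already registered. Support that with a match on data the article already collects: the child's birth date and sex, and household composition. A match should flag the registration for confirmation and not exclude it automatically, since these items can coincide by chance. A second caregiver may still receive the content without being randomized or counted toward the 260. It should be the version the first caregiver has, or the contamination returns.

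For any pairs already randomized, keep everyone in the primary analysis. Dropping second caregivers would conflict with the intention-to-treat commitment under Statistical analysis. Account for the shared child or household, for example with a household cluster term, and add a sensitivity analysis that keeps only the first registered caregiver, whose enrolment could not have depended on the partner's arm. Neither analysis reverses contamination that has already occurred.

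The cost is one eligibility sentence, one check in the app and a few second caregivers lost from the recruitment count. Because recruitment began in July 2021, this is a change during the trial and should go through the notification and registry update described under Data management.

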### Power and sample size

Statistical power analysis was performed for sample size estimation based on published data regarding this topic using G*Power 3.1.9.2. For our repeated measures within-between group comparison study, we used Cohen’s *f* criteria and considered a small effect size of 0.15 [8, 31], an alpha equal to 0.05, and power of 0.80 for a two-group with four repeated measures design (with a moderate correlation pattern between time measurements of 0.35). The sample size needed is approximately 130 participants (i.e., 65 parents in each of the two-arm groups), but the total sample size was adjusted to account for a dropout rate of 50% [32, 33]. Therefore, the sample will be collected until 130 participants in each group (*N* = 260) enroll in the study. Our proposed sample size will also be adequate for multilevel modeling with level 1 repeated measures nested within level 2 individuals, by assuring a minimum of 50 individuals required for level 2 [34].

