##### Parental feeding practices

Parental feeding practices are evaluated through the *Food Parenting Practices Questionnaire* [37]. The questionnaire includes three main components: *Promotion of children’s intake self-regulation practices* (e.g., item 9: “If the child says he/she wants to eat more but I think the child had enough, I encourage him/her to stop eating.”), *Food availability and accessibility practices* (e.g., item 23: “I include some form of fruit in most meals*.*”), and *Ineffective control practices* (e.g., item 33: “I withhold sweets/dessert from my child in response to bad behavior.”). Parents answer the 40 items on a 5-point Likert scale (from *Totally false* to *Totally true*). Higher values on each scale indicate more frequent use of each type of practice. In an online study with parents of 2- to 5-year-old Portuguese children, the parental feeding subscales’ internal consistency ranged between 0.65 and 0.89, with an inter-item correlation mean (IICM) between 0.30 and 0.74 [37]. The three scores regarding *promotion of children’s intake self-regulation practices*, *food availability and accessibility practices*, and *ineffective control practices* are studied as primary outcomes. Time points are as follows: baseline, immediately after the intervention, 3 months after the intervention, 6 months after the intervention.

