### Statistical analysis

We will use intention-to-treat principles, with the participants being analyzed in the group in which they were allocated in the randomization process, independently of whether they had completed all measurement time points and/or the intervention. First, an evaluation of missing data mechanisms will be performed to inform which imputation strategy should be applied between multiple imputations (MI) and maximum likelihood estimation (FIML). Assuming the data are missing at random, a sensitivity analysis will be included, considering the whole samples vs. samples with complete data separately.

A descriptive analysis of demographic data and outcome variables at baseline will be performed for parents’ and children’s characterization purposes; the samples in each condition group will also be compared for all dimensions studied. Repeated measures analyses will be used to analyze the differences between condition groups and measurement time points over time regarding primary outcomes, adjusting for potential covariates. To study parents’ dropout predictors, we will first assess the differences between completers, early and late dropouts regarding demographic data, and all variables at baseline. The relationships between parents’ and children’s dimensions with dropout rates will be assessed. We will then conduct a binomial logistic regression to predict the overall dropout. The analysis of individual health trajectories regarding parents’ and children’s variables evolution throughout the intervention will be studied using mixed models. The *p* value will be corrected according to the number of primary outcomes considered in each statistical analysis.

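### The 80% power is calculated for one test at alpha 0.05, while six primary outcomes are to be tested with corrected p values, so it is not the power of those tests

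*Protocol article*

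**What the plan says.** **Sizing** (Protocol article, Power and sample size). "For our repeated measures within-between group comparison study, we used Cohen’s *f* criteria and considered a small effect size of 0.15". The other inputs are "an alpha equal to 0.05, and power of 0.80 for a two-group with four repeated measures design"; the correlation assumed between any two assessments is 0.35. The result is about 130 parents, 65 per arm, raised to 260 for 50% dropout. The section says nothing about multiple primary outcomes.

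**Primary outcomes** (Children's dietary intake; Parental feeding practices). The mean portions of vegetables, of fruit, and of sugar-sweetened foods and beverages "will be extracted from the database and analyzed separately as primary outcomes". Three questionnaire scores (self-regulation promotion, food availability and accessibility, ineffective control) "are studied as primary outcomes". That makes six.

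**Testing** (Statistical analysis). "The *p* value will be corrected according to the number of primary outcomes considered in each statistical analysis". The correction method is not named.

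**The concern.** The sizing section and the analysis section give different significance levels for the same tests. Correcting for two or more outcomes means that at least some primary results are judged at a level below 0.05, yet the power was worked out at 0.05. A later plan could name the correction method, but it could not turn the corrected level back into 0.05 while keeping the rule as printed.

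What is at stake is how a single primary outcome is read. The Discussion itself expects that the active control may shrink the difference between arms, so null results on individual outcomes are plausible. A reader would weigh such a result against a stated 80% chance of detecting the planned effect, when the chance at the corrected level is a different figure that the protocol does not give.

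**Working it through.** **Inputs from the protocol.** f = 0.15, correlation ρ = 0.35, k = 2 groups, m = 4 time points, alpha 0.05, power 0.80, about 130 analysable parents.

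**Assumptions not in the protocol.** The sphericity epsilon (ε), and a Bonferroni correction with divisor 2, 3 (one outcome domain) or 6 (all primary outcomes): 0.05/2 = 0.025, 0.05/3 = 0.0167, 0.05/6 = 0.0083.

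**Formula** (G*Power, repeated measures, within-between interaction). Noncentral F with
- λ = ε·f²·N·m/(1−ρ)
- df1 = ε(k−1)(m−1)
- df2 = ε(N−k)(m−1)

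**Step 1: reproduce 130.**
- ε = 1: N = 82 is required, not 130.
- ε = 0.5: N = 130, with power 0.802.
- Other variants tried at alpha 0.05 and power 0.80: multivariate interaction test 84; interaction with ρ left out of λ 164 to 166; between-groups main effect 182.

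Of the variants tried, only ε = 0.5 gives 130. The dropout step reproduces: 130/(1−0.5) = 260.

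**Step 2: power at N = 130 at each level.**

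For ε = 0.5: λ = 0.5 × 0.0225 × 130 × 4/0.65 = 9.0, df = 1.5 and 192. For ε = 1: λ = 18.0, df = 3 and 384.

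| Alpha | ε = 0.5 | ε = 1 |
|---|---|---|
| 0.05 | 0.802 | 0.957 |
| 0.05/2 | 0.714 | 0.925 |
| 0.05/3 | 0.659 | 0.902 |
| 0.05/6 | 0.565 | 0.853 |

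Between these, ε = 0.75 (λ = 13.5, df = 2.25 and 288) gives 0.812 at 0.05/3 and 0.740 at 0.05/6.

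**Step 3: does the drop depend on how 80% was reached?** Fix the noncentrality so that power is exactly 80% at 0.05, then lower alpha:
- F test with 3 df: 65.9% at 0.05/3, 56.7% at 0.05/6
- F test with 1 df: 65.4% and 55.8%
- normal approximation: 65.8% and 56.5%

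So any test that truly has 80% power at 0.05 falls to about 66% and 57%. This holds only once the 80% at N = 130 is granted. It does not show that 130 parents do give 80%.

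**Step 4: smallest f detectable with 80% power at N = 130** (same formula solved for f).
- ε = 0.5: 0.150 at 0.05, 0.172 at 0.05/3, 0.185 at 0.05/6
- ε = 1: 0.117, 0.133 and 0.142

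**The case against.** The strongest reply is that no shortfall has been shown. The figures below 80% for three or six outcomes need an epsilon that the protocol does not print. Under sphericity the printed inputs need 104 parents at 0.05/3 and 118 at 0.05/6, both below 130, so even the strictest correction is covered. This stands as a limit on the size of the problem. The difficulty is that the same inputs then require only 82 parents, which does not fit the protocol's own figure of about 130. Either the epsilon was not 1, or the stated 80% is not the power of 130 parents even at 0.05.

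The divisor and method are also open. The rule refers to the outcomes in each analysis, and the dietary outcomes are analysed separately, so a divisor below three is a possible reading. With one outcome per analysis there would be no correction and the 0.05 would stand, but the sentence promising a correction would then do nothing for the primary tests. A step-down method would lose less power than Bonferroni, though its first step uses the same divisor.

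Finally, the analysis is by intention to treat with multiple imputation or full-information maximum likelihood, so parents who leave late still contribute data. With complete data on all 260, ε = 0.5 gives 0.950 at 0.05/3 and 0.919 at 0.05/6. True power lies somewhere between the 130 and 260 figures, depending on dropout timing that the protocol does not give. This also stands, although the protocol chose to size on 130.

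**Conclusion.** The mismatch in alpha holds: the 0.05 and 0.80 printed in the sample-size section do not describe the corrected primary tests.

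Its size is conditional. Accepting 80% at 0.05 with 130 complete cases (ε = 0.5) and assuming Bonferroni, power is about 71%, 66% and 57% for divisors of two, three and six. With ε = 1 it is about 90% for three and 85% for six. Partial data from dropouts would raise each figure.

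A reader might infer that the trial is underpowered, with little better than an even chance of detecting the planned effect on each outcome. The protocol does not support that. The 57% combines ε = 0.5, Bonferroni, a divisor of six and no information from dropouts. Nor can it be said that power at the corrected level always misses the stated figure: at ε = 0.75 it is 0.81 for a divisor of three. What can be said is that the power of the primary tests is not stated and cannot be worked out from what is printed.

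**What to change.** Keep N = 260. In the sample-size section:
- state the epsilon used;
- rerun the same G*Power calculation at the alpha actually applied to each primary outcome (0.05/3 or 0.05/6);
- replace the 0.05/0.80 statement with the resulting power at 130 analysable parents, or with the smallest effect detectable with 80% power at that level.

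The cost is one rerun and one or two sentences. No participants are added, and recruitment, design and analysis are unchanged. If ε = 0.5 was used, the reported power will look less favourable than the present 80%.

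### The 130 in the sample size paragraph does not follow from the inputs printed with it, and f = 0.15 for the group-by-time test is not a small between-arm difference

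*Protocol article*

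**What the plan says.** The calculation is in the Power and sample size section of the protocol article. The software is named: "Statistical power analysis was performed for sample size estimation based on published data regarding this topic using G*Power 3.1.9.2". The test is identified by "For our repeated measures within-between group comparison study", which points to the group-by-time interaction. The authors "considered a small effect size of 0.15" on Cohen's f scale, with "an alpha equal to 0.05" and "power of 0.80 for a two-group with four repeated measures design", and assume "a moderate correlation pattern between time measurements of 0.35". The result is "The sample size needed is approximately 130 participants (i.e., 65 parents in each of the two-arm groups", doubled to 260 for 50% dropout. No sphericity value is printed, and the effect is not expressed in SD or outcome units.

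Three other places bear on this:

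- Outcome measures names six primary outcomes: three dietary counts and three feeding-practice scores.
- Statistical analysis says the p value will be corrected for the number of primary outcomes in each analysis, without fixing the divisor. It also plans an intention-to-treat analysis with multiple imputation or FIML.
- The Discussion concedes of the active comparator that "it also can lead to a less-expressive difference between conditions".

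**The concern.** The paragraph prints inputs and a result together, so a reader should be able to get from one to the other. With the inputs as printed that fails by a wide margin: 130 is about 1.6 times the 82 they give. The input that closes the gap is not shown, and it decides how much room is left once the p value is corrected for several primary outcomes.

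The word small is a separate problem. For a two-group comparison of means, f is half the standardised difference, so f = 0.15 would be read as 0.30 SD. For a group-by-time interaction, f is the SD of the interaction cell effects, and the same 0.15 stands for a much larger difference between arms. A reader may take the trial as having 80% power for a small group difference and over-read a null result. The article itself expects the active comparator to narrow the contrast.

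**Working it through.** **Inputs** (Power and sample size section): f = 0.15, k = 2 groups, m = 4 measures, rho = 0.35, alpha = 0.05, power 0.80. Epsilon is not given.

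**Formula** (within-between interaction, noncentral F):

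- lambda = f² × N × m × eps / (1 − rho)
- df1 = (k − 1)(m − 1) × eps
- df2 = (N − k)(m − 1) × eps

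**1. Attempt to reproduce 130 with eps = 1.**

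- N = 80: lambda = 0.0225 × 80 × 4 / 0.65 = 11.08, df 3 and 234, power 0.7996.
- N = 82: lambda = 11.35, df 3 and 240, power 0.811. The required N is 82, or 164 after 50% dropout.
- N = 130: lambda = 18.0, df 3 and 384, power 0.957.

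**2. Other readings at the same f, alpha, power and rho.** The between-group test has lambda = 0.0225 × N × 4 / 2.05 and needs 182 (power at 130 is 0.66). The MANOVA approach needs 84. Alternative effect-size conventions give 124, 164, 166 or 486. None returns 130.

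**3. Adding epsilon = 0.5.**

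- N = 128: lambda = 8.86, df 1.5 and 189, power 0.795.
- N = 130: lambda = 9.00, df 1.5 and 192, power 0.802.

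This gives exactly 130. The dropout step then reproduces: 130 / (1 − 0.5) = 260. That epsilon was 0.5 is an inference. It fits poorly with a single common correlation, because equal correlations with equal variances imply eps = 1.

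**4. Effect of the planned correction.** The divisor is assumed to be 3 or 6. Power for f = 0.15 with 130 analysed:

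| Alpha | eps = 1 | eps = 0.5 |
|---|---|---|
| 0.05 | 0.957 | 0.802 |
| 0.05/3 | 0.90 | 0.66 |
| 0.05/6 | 0.85 | 0.57 |

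At eps = 1 the N needed for 80% power is 104 at 0.05/3 and 118 at 0.05/6.

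**5. What f = 0.15 means between arms.** Let D_j be the between-arm difference at time j in SD units, with D = 0 at baseline. Then f = ½ × √(mean of (D_j − mean D)²).

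- Present at two of three follow-ups, for example (0, 0, d, d): f = ½ × √0.25 × d = 0.25d, so d = 0.15/0.25 = 0.60.
- Constant (0, d, d, d): f = ½ × √0.1875 × d = 0.2165d, so d = 0.69.
- Linear growth (0, d/3, 2d/3, d): f = ½ × √0.1389 × d = 0.1863d, so d = 0.80 at 6 months.

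**6. Detectable constant difference, 80% power, alpha 0.05/6** (solve for f, then divide by 0.2165):

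| Analysed | eps = 1 | eps = 0.5 |
|---|---|---|
| 130 | 0.1423, i.e. 0.66 SD | 0.1847, i.e. 0.85 SD |
| 260, full information | 0.1002, i.e. 0.46 SD | 0.1299, i.e. 0.60 SD |

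**The case against.** The best defence is that a condensed article left out one software setting. The software takes epsilon as an input alongside the correlation, it accepts 0.5 with a correlation of 0.35, and it then returns 130 exactly. This stands to the extent that a reader might infer 130 is simply an arithmetic error, and the article does not support that. What it supports is that 130 cannot be reproduced from what is printed.

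A reader might also infer that the promised 80% power is not delivered. For the effect as the article defines it, f = 0.15 at alpha 0.05, that is false: power at 130 is 0.957 or 0.802. If epsilon was 1, the discrepancy is conservative and survives even a divisor of 6.

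A third tempting reading is that the trial is badly underpowered for a difference of about 0.30 SD. For a constant 0.30 SD difference at eps = 1 and alpha 0.05, power is 0.30 with 130 analysed and 0.57 with 260. But 0.30 SD is nowhere in the article as a target, so this cannot be charged against the plan. Whether f = 0.15 was a sound target rests on cited reviews that are not available here.

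Finally, figures based on 130 analysed are the pessimistic end. The analysis is intention-to-treat with imputation or FIML, so participants with partial data contribute. By the formula above, if all 260 gave full information, power for f = 0.15 at eps = 0.5 would be 0.95 at 0.05/3 and 0.92 at 0.05/6. The truth lies between the two ends.

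What remains after these objections is the missing input, the uncorrected alpha and the label small.

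**Conclusion.** The point holds as a reporting correction to a figure the trial relies on. It does not show a design failure.

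- **The number.** The printed inputs give 82, not 130. Either 130 is larger than those inputs require, or an unprinted epsilon of 0.5 was used.
- **The power.** If epsilon was 0.5, the 80% with 130 analysed does not survive the article's own multiplicity correction: 0.66 at 0.05/3 and 0.57 at 0.05/6. If epsilon was 1, power is 0.90 and 0.85. Both divisors are assumptions, because the article fixes none.
- **The label.** For this interaction, f = 0.15 is a between-arm difference of about 0.60, 0.69 or 0.80 SD, depending on the pattern over follow-up. This assumes equal baselines and a common SD across time points. It should not be presented as a small group difference.

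**What to change.** Keep N = 260 and restate the Power and sample size paragraph:

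1. State the epsilon that was used, with its justification, or replace 130 by the figure the printed inputs give.
2. Fix the multiplicity divisor and run the calculation at that alpha.
3. Replace the word small with the detectable between-arm difference in SD units. State the assumed pattern over time, epsilon, alpha and number analysed. For a constant difference at 0.05/6 with 80% power, this is about 0.66 SD (epsilon 1) or 0.85 SD (epsilon 0.5) with 130 analysed. It is about 0.46 or 0.60 SD if all 260 contribute full information. Print only the values that match the epsilon declared in step 1.

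The cost is one rewritten paragraph, with no extra participants and no change to the design. The downside is that the stated sensitivity will look less favourable than it does now.
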